## Abstract

**Background:**

Recent developments suggest that neurosteroids may achieve rapid antidepressant effects. As such, neurosteroidogenesis mediated by the translocator protein 18 kDa (TSPO) might constitute a promising option for the treatment of depression. Therefore, the current clinical trial aims to get the first evidence of whether TPSO ligands promote rapid antidepressant effects. Furthermore, we study which mechanisms of action, e.g., modulation of distinct neuronal networks, neurosteroidogenesis, endocrinological mechanisms, TSPO expression or microbiome composition, contribute to their putative antidepressant effects.

**Methods:**

This is a randomized, placebo-controlled, double-blind single-center trial of 2-week treatment with the TSPO ligand etifoxine versus placebo in depressive patients. Main eligibility criteria: male or female individuals aged 18 to 65 years with unipolar/bipolar depressive disorder with no other psychiatric main diagnosis or acute neurological/somatic disorder or drug/alcohol dependence during their lifetime.

The primary endpoint is the time point at which 50% of the maximal effect has occurred (ET50) estimated by the scores of the Hamilton Depression Scale (HAMD-21). A total of 20 patients per group are needed to detect changes of therapeutic efficacy about 5% and changes of ET50 about 10% with a power of 70%. Assuming a drop-out rate of 10–20%, 50 patients will be randomized in total. The study will be conducted at the Department of Psychiatry and Psychotherapy of the University of Regensburg.

**Discussion:**

This study will provide a first proof-of-concept on the potential of the TSPO ligand etifoxine in the treatment of depressive disorders.

**Trial registration:**

Clinical Trials Register (EudraCT number: 2021-006773-38, registration date: 14 September 2022) and German Register of Clinical Studies (DRKS number: DRKS00031099, registration date: 23 January 2023).

## Administrative information

Note: the numbers in curly brackets in this protocol refer to SPIRIT checklist item numbers. The order of the items has been modified to group similar items (see http://www.equator-network.org/reporting-guidelines/spirit-2013-statement-defining-standard-protocol-items-for-clinical-trials/).

## Introduction

### Background and rationale {6a}

Neurosteroidogenesis mediated by the translocator protein 18 kDa (TSPO) [1–4] plays an important role for psychiatric disorders and their treatment. Meanwhile, numerous studies have shown altered expression of TSPO in psychiatric disorders [5, 6]. These studies targeted either the expression of TSPO mRNA in peripheral mononuclear cells, the binding characteristics of the TSPO ligand PK11195 to platelet membranes, or protein expression in thrombocytes [7–9]. Various positron emission tomography (PET) studies reported increased TSPO expression in depression [10, 11]. It has even been suggested that TSPO PET imaging may predict the clinical response to celecoxib treatment in major depression [12]. Moreover, in depression with cognitive impairment upregulation of TSPO labeling has been reported using PET [11]. Gene variants such as the rs6971 TSPO polymorphism, which affects ligand binding and cholesterol uptake, were found to be linked to both bipolar disorder in general and diurnal cortisol rhythm in bipolar disorder [13, 14]. Therefore, it should be considered in clinical trials when assessing TSPO binding or function.

Various TSPO ligands have been shown to exert acute anxiolytic/anti-conflict activity in rodents [2, 6, 15]. In a translational study, the selective TSPO ligand XBD173 enhanced GABAergic neurotransmission in brain slices via the induction of neurosteroidogenesis and effectively reduced the number of pharmacologically induced panic attacks in rodents in the absence of sedation [15]. Moreover, XBD173 displayed anti-panic and anxiolytic efficacy in humans using an experimental anxiety paradigm involving a challenge with cholecystokinin tetrapeptide. Noteworthy, sedation and withdrawal symptoms occurring for benzodiazepines were absent in the XBD173-treated subjects after 7 days of treatment. A recent animal study suggested that the TSPO ligand AC-5216 (XBD173) may exert rapid antidepressant and memory-enhancing effects [16]. The capability of TSPO ligands to exert anxiolytic and antidepressant effects has also been demonstrated for other novel TSPO ligands such as YL-IPAo8 in a rat model of postpartum depression [17] or the antagonistic ligand ONO-2952 [18]. As such, TSPO may represent a promising target for the development of fast-acting anxiolytics and anti-depressants with a favorable side effect profile.

Currently, the only clinically available TSPO ligand is etifoxine (Stresam, Biocodex), which has been approved for the treatment of anxiety disorders in France. Etifoxine has a dual mode of action, as it targets TSPO but also directly α2 and α3 containing GABA(A) receptors [19]. Initial clinical trials with etifoxine have provided the first evidence for a clinical anxiolytic effect of etifoxine showing comparable efficacy to the benzodiazepine lorazepam in patients suffering from adjustment disorders with anxiety [20]. The anxiolytic effects of etifoxine are comparable to clonazepam and have recently been confirmed in a randomized controlled double-blind clinical trial in patients with anxiety disorder [21].

GABAergic modulators such as benzodiazepines are known to inhibit long-term synaptic potentiation necessary for memory formation [22]. Using functional magnetic resonance imaging (fMRI) and an acute challenge with the benzodiazepine lorazepam in healthy participants, it was found that blood oxygenation level-dependent (BOLD) responses in the amygdala to novel stimuli were attenuated, which is in line with the known risk of benzodiazepines causing anterograde amnesia [23]. However, it is unknown whether or to which degree TSPO ligands such as etifoxine, which may also target extrasynaptic GABA(A) receptors by means of endogenous neurosteroidogenesis [19, 24], affect learning and memory. To this aim, we developed an event-related version of the face-name-association (FNA) task employed by Sperling et al. [23]. This task allows us to trace the neural signature of novel stimuli during memory acquisition on a trial-by-trial basis and to characterize the efficiency of learning by the slope BOLD amplitude as a function of a number of stimulus repetitions.

Antidepressant treatment is related to neural, cognitive, and emotional changes in patients. It has been demonstrated that fMRI in combination with a multivariate technique, a so-called representational similarity analysis (RSA), is able to assess the neural representation of an individualized relational affective space [25]. Recently, it could be shown how RSA can be employed in psychiatry to assess the commonalities in cognitive-emotional and neural changes in the context of interventions in mental disorders [26].

Because also bacteria express TSPO and bacterial TSPO shares structural and functional characteristics with mammalian TSPO [27], TSPO ligands may also affect microbiome composition. So far, it could be shown that short-term etifoxine intervention reduces the abundance of a few bacterial species, which are currently seen as beneficial components of a healthy intestinal microbiome. This reduction may be mainly related to elevated endogenous neurosteroids [28].

Another promising approach is the direct application of neurosteroids such as the intravenous formulation of brexanolone [29] or the oral administration of zuranolone (SAGE-217) [30]. Intriguingly, these compounds may exert quite rapid antidepressant effects. While brexanolone and zuranolone have recently been approved for the treatment of postpartum depression by the FDA, the antidepressant properties of zuranolone are currently being investigated in a series of multicenter studies and still await approval by the FDA. These recent developments and the discrete neuroinflammation reported in depression have promoted the idea that TSPO ligands may constitute an attractive alternative to exogenous neurosteroids in the treatment of depression [6]. Therefore, the current clinical trial aims to get the first evidence of whether the TPSO ligand etifoxine may confer rapid antidepressant effects and which mechanisms of action, e.g., modulation of distinct neuronal networks, neurosteroidogenesis, HPA axis activity, TSPO expression and of microbiome composition, contribute to its putative antidepressant effects.

### Objectives {7}

#### General objective

Within this clinical trial, we will investigate whether the administration of the TSPO ligand etifoxine in addition to treatment as usual (TAU) changes the time course or the extent of the therapeutic response in patients with severe unipolar/bipolar depression. Besides clinical effects as well as physiological and endocrine markers, we will assess the impact of the treatment on neuronal networks. Furthermore, changes of microbiome composition will be studied.

#### Primary objective

The primary objective of the trial is to investigate the effects of add-on treatment with etifoxine on clinical symptoms in patients with severe unipolar/bipolar depressive disorder. Clinical symptoms will be assessed using the Hamilton Depression Scale (HAMD-21) [31] up to day 15 after the start of the treatment.Does add-on treatment with the TSPO ligand etifoxine in addition to TAU for 14 days fasten the treatment response (decrease of ET50; ET50 = time point at which 50% of the maximal effect has occurred) in comparison to placebo?

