### Sample size {14}

The calculation of the sensitivity of the planned analyses is based on recent work, which investigated the effects of treatment with SAGE-271 (zuranolone) compared to placebo in patients with the depressive disorder [30]. We used least squares approximation to estimate the parameters of an Emax model [46] considering the scores of the HAMD-21 reported by Gunduz-Bruce and colleagues. This resulted in Emax TAU + PLC = 0.586 and ET50 TAU + PLC = 4.224. This means that comparable TAU with an additional placebo would lead to a reduction of the HAMD-21 scores of 58.6% and that half of this decrease would be reached after slightly more than four days.

Montecarlo simulations of an Emax model based on the mentioned parameter estimations for TAU and on the reported standard deviation of the HAMD-21 scores with s = 2.6 in the study of Gunduz-Bruce et al. [30] show that a sample size of 20 patients per group (TAU + placebo, TAU + etifoxine) is sufficient to detect chances of therapeutic efficacy (Emax) of about 5% and changes of the response latency (ET50) of about 10% with a statistical power of 70%. Assuming a drop-out rate of 10–20% we plan to recruit in total of 50 patients (25 per group).

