## Data collection and management

### Plans for assessment and collection of outcomes {18a}

The primary outcome parameter is ET50 estimated using the Hamilton Depression Scale (HAMD-21) scores collected on baseline day and on days 1, 2, 3, 4, 5, 6, 7, 8, 15, 22, and 29 of treatment. To guarantee good quality of the assessment, we have designated a fixed team of raters that were internally trained by experienced psychiatrists with a focus on high inter-rater consistency. Additionally, all ratings for one patient will consistently be performed by the same rater. For a description of all other outcome parameters see {12}.

A web-based, electronic Case Report Form (eCRF) within a validated database management system is used for the database-supported recording of study data. This system enables consistent data storage and quality control. Qualified entry personnel are given access to the eCRF by assigning personal login data. A medical investigator confirms timely with an electronic signature that the study data was entered into the database completely and correctly.

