## Statistical methods

### Statistical methods for primary and secondary outcomes {20a}

Statistical analyses will be conducted by the Center for Clinical Studies, University of Regensburg in collaboration with the Biomedical Imaging group of the Department of Psychiatry and Psychotherapy, University of Regensburg. We will use SAS (version 9.4 or higher), Matlab (version 2021a or higher), R (R Core Team, 2020), and scikit-learn (1.3.2 or higher) for the analyses.

Baseline characteristics and demographic data will be presented descriptively for all patients and separately for the two treatment groups. Categorical variables will be reported by absolute and relative frequencies, interval scaled data using descriptive values like mean, standard deviation, median, interquartile range, minimum, and maximum.

Primary endpoint: Using the Nelder-Mead Simplex method (implemented in Matlab) we will conduct a nonlinear minimization of the square deviation of the HAMD-21 scores from an Emax function with the free parameters Emax and ET50 for each patient. Emax and ET50 will be tested each per t-test for mean value differences between TAU + Placebo and TAU + Etifoxine.

Secondary endpoints: All secondary endpoints will be analyzed only exploratory and will be defined in detail in the Statistical Analysis Plan. There will be no multiplicity adjustments of the *p*-values.

Safety endpoints: All data concerning the safety of the investigational product will be listed and reported in comparison to placebo. All (serious) adverse events will be summarized in frequency tables and will further be reported separatly according to intensity and relation to the investigational product.

Imaging data will be analyzed using specialized software (FSL, http://fsl.fmrib.ox.ac.uk) and with own Matlab- and Python-based programs. In all conducted tests we make no assumptions on the distribution of the data and therefore use computer-based randomization tests for the evaluation of significance.

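### A lower ET50 alone counts as a faster response, but ET50 can also fall when the plateau shrinks, so a drug that is worse at every visit could meet the primary objective as worded

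*Protocol article*

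**What the plan says.** The primary objective asks whether add-on etifoxine will "fasten the treatment response (decrease of ET50; ET50 = time point at which 50% of the maximal effect has occurred") compared with placebo, with symptoms followed to day 15. Section {18a} confirms the single criterion: "The primary outcome parameter is ET50 estimated using the Hamilton Depression Scale (HAMD-21) scores", and lists visits to day 29.

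Section {20a} fits, by least squares, "an Emax function with the free parameters Emax and ET50 for each patient", then compares the arms by a separate t-test on each parameter. The secondary objectives list Emax and the day-15 HAMD-21 score, and {20a} calls all secondary endpoints exploratory.

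Section {14} supplies the reference curve: "This resulted in Emax TAU + PLC = 0.586 and ET50 TAU + PLC = 4.224". It explains the Emax value as treatment that "would lead to a reduction of the HAMD-21 scores of 58.6" per cent, so a larger Emax is the better outcome. No sentence makes the ET50 conclusion depend on the size of the response.

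**The concern.** ET50 measures time against a yardstick that each patient's own fit supplies. If the early response is kept and the later response is lost, half of the smaller maximum is reached sooner and ET50 drops, although no patient improves sooner in HAMD-21 points. The reverse also holds: a drug that keeps the early slope and reaches a higher plateau has a longer ET50.

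The trial wants first evidence of rapid antidepressant action. As worded, its primary conclusion could be reached by a treatment that lowers HAMD-21 less on every rating day, or missed by one that lowers it more on every rating day.

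**Working it through.** **Inputs from the protocol.** Placebo-arm Emax 0.586 and ET50 4.224 days; "reported standard deviation of the HAMD-21 scores with s = 2.6"; "a sample size of 20 patients per group"; visits on days 1–8, 15, 22 and 29 ({18a}).

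**Assumptions, because the protocol does not give them.** Curve E(t) = Emax·t/(t + ET50), where E is the fractional HAMD-21 reduction; two-sided 5% level; mean baseline 25 (entry requires more than 18); the SD of 2.6 read as independent noise at each visit.

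**The plan's own figures.** 20/(1 − 0.2) = 25 per group, which reproduces the 50 randomized. The sensitivity claim, "changes of the response latency (ET50) of about 10% with a statistical power of 70" per cent, can be neither confirmed nor refuted without the level, sidedness, baseline mean and variance structure. With 2.6 as per-visit noise, simulated two-sided power for a 10% shorter ET50 is 3–9% over baselines of 20–30. With 2.6/√20 = 0.58 it is 30–90%, and about 74–76% at baseline 25 with visits to day 29. The point below does not depend on which is right.

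**Step 1: algebra.** Let placebo have (A, B) and the drug (a, b) for (Emax, ET50). The drug is worse at time t when a(t + B) < A(t + b), that is, when (a − A)t + (aB − Ab) < 0. If a < A and a/b ≤ A/B, this holds for every t > 0. Any such drug with b < B is worse throughout and has the lower ET50. The placebo slope is A/B = 0.586/4.224 = 0.1387 per day.

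**Step 2: numbers, with the initial slope held at 0.1387.** ET50 = Emax × 4.224/0.586. The last column is the time to a fixed 29.3% reduction (half the placebo maximum), ET50 × 0.293/(Emax − 0.293).

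| Emax; ET50 (days) | ET50 vs placebo | Day 3 | Day 8 | Day 15 | Days to 29.3% |
|---|---|---|---|---|---|
| 0.586; 4.224 (placebo) | – | 24.3% | 38.4% | 45.7% | 4.22 |
| 0.40; 2.88 | 32% shorter | 20.4% | 29.4% | 33.6% | 7.90 |
| 0.527; 3.80 | 10% shorter | 23.3% | 35.8% | 42.1% | 4.75 |
| 0.75; 5.41 | 28% longer | 26.8% | 44.8% | 55.1% | 3.47 |

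In each row ET50 points one way, while the HAMD-21 course and the time to a fixed improvement point the other.

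**Step 3: the limit.** If Emax is halved and ET50 stays at 4.224 days, the whole curve shrinks in proportion. A significantly lower ET50 then appears in only 0–2% of simulated trials.

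**Step 4: how often under the planned t-test.** Simulated trials with 20 per group and per-patient least-squares fits. Drugs with Emax 0.40 or 0.30 and the placebo initial slope show a significantly lower ET50 in:
- about 5–9% of trials with SD 2.6 and visits to day 15 (the primary objective's horizon);
- about 28–38% with SD 2.6 and visits to day 29 (the {18a} list); repeat runs ranged from 25 to 41%;
- essentially all trials with noise of 0.58, in either window.

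For the mild case (0.527; 3.80), with noise 0.58 and visits to day 29, the figure is 67%. That is close to the power for a true 10% shortening with Emax unchanged.

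**The case against.** The strongest reply is that the protocol defines ET50 openly as latency relative to the maximal effect and asks about extent separately. Emax is tested beside ET50, and the day-15 score has its own objective. In simulation with SD 2.6, the drugs with Emax 0.40 and 0.30 were significantly worse at day 15 in 95–100% of trials. Of the trials with a significantly lower ET50, 96–100% also showed that day-15 deficit. This stands: a reader might infer that the harm would go unseen, and the planned analyses do not support that. What remains is that those analyses are exploratory and nothing links them to the primary conclusion. The secondary objective on Emax also asks about a decrease, which, taken with the definition in {14}, would be a worse result.

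A reader might also infer that ET50 falls whenever the maximal effect shrinks. It does not; step 3 shows the exception. The effect needs a particular shape, with the plateau losing more than the early response, and nothing in the protocol suggests that etifoxine behaves this way.

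Finally, joint interpretation could be left to the analysis plan. But the primary parameter and the meaning of its direction are fixed in this document, and {20a} defers only the secondary endpoints.

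**Conclusion.** The point holds in this form: as worded, the primary objective can be met by a drug that is worse at every visit, and missed by one that is better at every visit. That follows from the algebra and the placebo values in {14}, given the standard Emax curve. How often it would happen is uncertain. The planned-test figures run from about 5–9% to nearly all trials, depending on the fit window and the noise, and they rest on an assumed baseline of 25 and an assumed 5% two-sided level. They describe hypothetical drugs with a marked loss of plateau and are not a forecast for etifoxine. This is a gap in the decision rule; it does not mean that ET50 is unusable. It should be corrected before unblinding.

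**What to change.** Keep ET50 as the primary parameter. State in {7} and {20a} that a faster response is concluded only if ET50 is significantly lower and the HAMD-21 reduction at day 15 is not significantly smaller on etifoxine. Report the ET50 result together with the mean HAMD-21 curves and their differences with 95% confidence intervals at days 3, 8 and 15. Reconcile the direction of Emax in the secondary objectives with {14}.

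The cost is wording and a slightly stricter claim; all the data are already scheduled. In simulation the day-15 condition cut false 'faster' conclusions for the clearly inferior drugs to 0–1% and cost essentially no power. Fitted Emax could replace the day-15 score as the condition, but the day-15 score needs no extrapolation: at ET50 4.224 only 15/19.224 = 78% of Emax is reached by day 15.

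The rule has a limit. A non-significant day-15 difference does not show equality, so with noisy data a small loss can pass, which is why the curves must be reported. Requiring the point estimates at days 8 and 15 to favour etifoxine would be stricter but dearer. At the 10% design effect it lowers success from about 74% to 66% (noise 0.58, visits to day 29), and with SD 2.6 the condition is met in only about 40% of trials.

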#### Secondary objectives

Does add-on treatment with etifoxine compared to placebo in addition to TAU in depressive patients lead to.A decrease of the Emax (= maximum effect which can be expected from the drug)?A reduction of the HAMD-21 score on day 15?Changes of the synthesis of neurosteroids, TSPO expression or activity of the hypothalamic–pituitary–adrenal axis?Changes in cognitive functions like memory or emotional processing assessed with a neuropsychological test battery?Changes of functional neuronal networks and cognitive functions assessed using fMRI applying resting state measurements and two tasks ((representational similarity analysis) RSA and face-name-association (FNA))?Changes of the microbiome composition?A relapse or withdrawal symptoms after discontinuation of the intake?

### Trial design {8}

This is a single-center, randomized, parallel-group, placebo-controlled, double-blind investigator-initiated superiority clinical trial (IIT) with two arms. Eligible patients will receive either etifoxine or placebo for a period of 14 days. The patient allocation ratio is 1:1. Measurements will be taken up to 29 days after the start of the study treatment. The trial will be conducted with 50 patients suffering from unipolar/bipolar depressive disorder.

## Methods: participants, interventions, and outcomes

### Study setting {9}

The trial will be performed at the Department of Psychiatry and Psychotherapy of the University of Regensburg in Germany. It is an acute psychiatric clinic providing the highest level of care with 475 inpatient treatment places and outpatient care for psychiatric patients. Affective disorders account for the second largest number of inpatient admissions at the clinic meaning that a correspondingly large number of patients can be expected.

